### Secondary outcomes

#### Physical activity

*Self-reported physical activity* is measured through eight questions from the Yale Physical Activity Survey (YPAS)
[33]. The questions measure the participant’s physical activity over the previous week undertaking exercise, household and recreational activities. Moderate to high validity and reliability have been established in a number of studies
[34,35].

*Exercise adherence data* is obtained from the researcher’s data sheets recorded on paper during phone calls and home-based participants’ self-report exercise logs, which provide important information about whether participants are exercising at home.

*Objective step data* is collected at baseline (7 days of step data – minimum of 3 days required) to determine any baseline differences and at each phone call timepoint.

### Functional ability

The Tinetti gait and balance test for agility is assessed at baseline and week 12, this tool is a reliable and valid clinical test to measure gait and balance in older people and other patient populations
[36]. The Tinetti was found to have the best predictive validity for fall risk in elderly people when compared to the timed up and go, functional reach test and one-leg stance test. The test is easily administered and provides information about an individual’s ability to ambulate and transfer safely
[36].

Ankle range of motion using a goniometer (Baseline plastic 360°) is used for collecting data on range of motion (ROM) of the ankle joint using a standardised protocol across sites. Participants are tested for ankle plantar flexion and dorsiflexion at baseline and 12 weeks after recruitment. Participants are asked to maximally perform ankle dorsiflexion and plantarflexion; the clinician then adds the two scores for the total range of ankle motion.

Lawton’s Instrumental Activities of Daily Living (IADL). The instrumental activities of daily living are assessed at baseline and week 12. These activities are more complex than basic activities of daily living, and being able to perform them allows a person to be independent within a community. The survey is designed to assess a patient’s everyday functional competence with consideration to housework, tasks involving mobility, managing the home and property; catching the bus; cooking meals and going shopping, use of medicine and financial behaviour
[37]. Few studies have tested the psychometric properties of the Lawton IADL scale, although it has been used for almost 40 years. Lawton and Brody originally determined acceptable levels of inter-rater reliability and construct validity for the Lawton IADL scale by examining its correlation with other scales that measure functional competence.

### Health-related quality of life

SF-8™ Health Survey1Medical Outcomes Survey Short Form-8 questionnaire (SF-8) is measured at baseline and week 12, it is a widely used, valid and reliable measure to assess health related quality of life
[38].

The MOS Social Support Survey is measured at baseline and week 12, it examines the perceived social support available to patients and represents the multiple dimensions of support including emotional, tangible, affectionate, and positive social interaction
[39].

The Geriatric Depression Scale (GDS) is measured at baseline and week 12, it is used to assess depressive symptoms over the last four weeks
[40]. The five-item GDS has been validated as an effective screening tool of depression in cognitively intact older subjects
[41] and reliable in a variety of settings
[42].

The Medical Outcomes Study (MOS) Pain Measures is measured at baseline and week 12, it is a valid and reliable means of assessing intensity, frequency and duration of pain on behaviour and mood
[43].

### Psychosocial beliefs toward exercise

Self-efficacy for Exercise scale is measured at baseline and week 12, it asks the participants about their confidence in performing exercise in a number of different circumstances
[44] that has been previously validated in older populations.

The Outcome Expectancies for Exercise Scale is measured at baseline and week 12, d and has been included in this analysis due to the importance of including outcome expectations, especially with older adults when measuring self-efficacy
[45].

Fear-Avoidance Beliefs Questionnaire (FABQ)
[46] is measured at baseline and week 12. The FABQ is a sixteen item self-report questionnaire aimed at quantifying the beliefs of how work and physical activity affect pain and whether they should be avoided. The two subscales, fear-avoidance beliefs for work (FABQ-work) and fear-avoidance beliefs for physical activity (FABQ-physical), this scale has been used previously in venous leg ulcer patient populations
[47].

### Data analysis

Differences in primary and secondary outcomes between groups will be compared using intention to treat analysis. Once a participant is randomised to a study group, they will be considered a trial participant and analysed according to their allocated group, regardless of missing data for follow ups or the amount of intervention received. Bivariate relationships will be tested with Pearson or Spearman correlations, independent t-tests or Mann–Whitney U tests to examine relationships between the dependent variables and the independent variables or chi square for categorical varibales. Each primary and secondary outcome will be modelled using mixed linear models to determine differences between groups and adjust for potential confounders. Potential confounders such as baseline characteristics, for example disease severity, ulcer size and/or duration etc. will be included and controlled for in the final model. Data analysis will be performed using SPSS v21. Statistical significance will be set at p < 0.05 for all analyses.

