### Randomisation and blinding

After completing all baseline data collection measures, participants are randomised to either intervention group protocols or control group protocols for 12 weeks or until healed. Participants in the intervention group receive evidence based wound care, and a VaLUE pack which includes a pedometer, general advice for looking after their legs and an information sheet. In addition those in the intervention group receive an instructor developed exercise booklet ‘VaLUE your Independence’, along with a verbal explanation and demonstration of the resistance exercise program. Those in the intervention are followed up by the first author for telephone exercise coaching at week one, two, four, six eight and twelve. Participants in the control group will also receive a VaLUE pack which includes a pedometer and the same general advice information sheet for looking after your legs.

The randomisation schedule has been prepared by an assistant independent to the research project using a computer generated random numbers table. To conceal randomisation, the independent staff member prepared consecutively numbered, sealed, opaque envelopes for each site. The envelopes are kept in a locked location at each site accessible only by an unblinded researcher. As VaLUE is a self-administered intervention, blinding of the participant and the researcher who conducts the telephone follow-up is by necessity unblinded.

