### Primary outcome measures

*Incidence of complete wound closure* at the completion of the study (12 weeks after initiation of exercise intervention). Wound photographs and tracings are collected fortnightly or monthly by the wound care nurses via the use of acetate grids and Visitrak for planimetry (Smith & Nephew Medical Limited, Hull, England) to determine: ulcer area and fortnightly percent reduction in area; time to healing; and incidence of complete wound healing. Healing is defined as full epithelialisation of the ulcer which has been maintained for at least two weeks without breakdown. Visitrak has been validated as a reliable measure of ulcer size with high intra-inter reliability
[30]. The Pressure Ulcer Scale for Healing (PUSH)
[31] tool is a standardised method of assessing and monitoring the severity of both pressure ulcers and venous leg ulcers using the following parameters: length, width, amount of exudate and wound bed tissue type to track healing progress over time. The PUSH tool has established psychometric properties, such as validity and sensitivity for venous wounds
[32].

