### Sample size calculations and expected loss to follow up

The sample size estimation was based on wound healing data from our pilot study and an estimated post-intervention difference in healing between groups. A sample of 44 participants randomised to each group will be sufficient to detect a moderate effect size difference (80% power and a 5% significance level) of 20% difference in proportions of healed ulcers between groups after a 12 week exercise intervention. This figure rises to 55 in each group to allow for a 20% loss to follow-up.

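### One mixed linear model is assigned to every outcome, but time to healing is right-censored and complete closure is a single yes/no value, so the stated model does not fit either

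*Protocol article*

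**What the plan says.** All references are to the protocol article; no separate analysis plan is shown.

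- **Data analysis.** The adjusted group comparison is fixed in one sentence: "Each primary and secondary outcome will be modelled using mixed linear models to determine differences between groups and adjust for potential confounders". Baseline characteristics such as disease severity, ulcer size and duration are to enter the final model. An earlier sentence lists bivariate tests, including chi-square for categorical variables. No logistic, other binary or survival regression is named. The section also commits to analysing everyone randomised in the allocated group, whatever follow-up is missing.
- **Primary outcome measures.** The lead outcome is "Incidence of complete wound closure" at 12 weeks. Tracings and photographs are then used "to determine: ulcer area and fortnightly percent reduction in area; time to healing; and incidence of complete wound healing". Healing is a state that is either reached or not: "Healing is defined as full epithelialisation of the ulcer which has been maintained for at least two weeks without breakdown".
- **Randomisation and blinding.** Participants follow intervention or "control group protocols for 12 weeks or until healed".
- **Sample size calculations and expected loss to follow up.** The trial is sized on a 20% "difference in proportions of healed ulcers between groups after a 12 week exercise intervention", with 44 per group raised to 55 for 20% loss.

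**The concern.** The difficulty is a rule that the document states, not a detail it leaves out. A single Gaussian model is assigned to outcomes of three types: repeated continuous measures (ulcer area, scores), a binary endpoint and a censored time.

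For time to healing, an ulcer still open at week 12 supplies only the information that its healing time exceeds 12 weeks, and a participant lost earlier supplies even less. A linear model cannot use a statement of that kind. The analyst must drop such participants, which conditions on the outcome, or enter an invented number.

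For closure, a 0/1 value has a variance that depends on its mean, a straight-line fit can leave the 0–1 range once covariates are added, and one value per person cannot support a within-person random effect.

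At stake are the power and meaning of the time-to-healing comparison and the specification of the adjusted closure analysis. There is also a risk that the real model is chosen after the data are seen, since the article reports the trial as already in follow-up.

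**Working it through.** **Inputs from the document:** 12-week follow-up; 44 per group before loss; 20% difference in proportions healed; 20% loss; 5% significance level. The plan's loss adjustment reproduces: 44 / (1 − 0.20) = 55. I take 44 as given; nothing below depends on whether it follows from the stated effect.

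**Assumptions, because the document gives no control healing rate or distribution:** constant healing hazard; 12-week healing of 50% v 70%, and as a second case 30% v 50%; two-sided 5% test; no loss before week 12.

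**Time to healing, three analyses of the same data**

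Hazard λ = −ln(1 − p)/12. For 50% v 70%: λ = 0.0578 and 0.1003, hazard ratio 1.74. For 30% v 50%: λ = 0.0297 and 0.0578, hazard ratio 1.94. Power = Φ(δ − 1.96) + Φ(−δ − 1.96), where δ is the difference divided by its standard error.

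1. *Healed ulcers only.* Mean = 1/λ − 12e^(−12λ)/(1 − e^(−12λ)). For 50% v 70%, the means are 5.31 and 4.82 weeks and the SDs 3.42 and 3.34, with 44 × 0.5 = 22 and 44 × 0.7 = 30.8 healed. SE = √(3.42²/22 + 3.34²/30.8) = 0.946; δ = 0.49/0.946 = 0.52; power 8.1%.
2. *Unhealed set to 12 weeks.* Mean = (1 − e^(−12λ))/λ, giving 8.66 and 6.98 weeks, SDs 4.13 and 4.32. SE = √((4.13² + 4.32²)/44) = 0.900; δ = 1.68/0.900 = 1.86; power 46%.
3. *Log-rank.* Events = 22 + 30.8 = 52.8; δ = ln(1.737) × √52.8 / 2 = 2.01; power 52%.

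| 12-week healing | Healed only | Unhealed = 12 weeks | Log-rank |
|---|---|---|---|
| 50% v 70% | 8% | 46% | 52% |
| 30% v 50% | 6% | 42% | 50% |

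In the second case δ is 0.33/1.198 = 0.28, then 1.44/0.813 = 1.77, then ln(1.943) × √35.2 / 2 = 1.97.

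Column two assumes complete follow-up. For someone lost at, say, week 4, entering 12 weeks assumes non-healing, entering 4 weeks treats loss as healing, and omission discards the observed ulcer-free-of-healing time. A censored analysis uses exactly what was observed.

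**Binary closure**

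With one value per person, the mixed model reduces to an ordinary linear model on 0/1 data. This was compared with logistic regression by simulation: 55 per arm, one standard normal prognostic covariate with log odds ratio −1.2, 1,500 runs per setting, intercepts 0 and 1.

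| Quantity | Linear | Logistic |
|---|---|---|
| Type I error | 5.7%, 5.3% | 5.7%, 5.5% |
| Power, treatment log odds ratio 0.95 | 54%, 46% | 54%, 45% |

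The simulation error at 5% is √(0.05 × 0.95/1500) = 0.6 percentage points, so both methods hold their size. In the linear fits, 4% to 10% of fitted probabilities fell outside 0–1.

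**The case against.** Several points on the other side stand.

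- **The binary test survives.** A reader might infer that the primary closure result would be invalid. The simulation does not support that: size and power are kept, and the out-of-range values are individual predictions, which the trial does not set out to report.
- **The scale agrees with the sizing.** A reader might also infer that a linear model fails to match the sample size basis. The reverse is true. Its coefficient on a 0/1 outcome is a difference in proportions, the quantity used for sizing; a logistic odds ratio alone would not match.
- **A suitable unadjusted test is listed.** Chi-square appears in Data analysis and is valid for healed v not healed. It is part of the bivariate step and does not supply the adjusted comparison.
- **8% v 52% is the worst case.** It requires dropping all unhealed participants, which the intention-to-treat commitment speaks against. Entering 12 weeks costs only about 6 to 8 percentage points with complete follow-up, and then estimates an interpretable restricted mean difference over 12 weeks. That defence weakens once participants leave early.
- **Time to healing is not the lead outcome.** It is one of the measures under the primary heading; incidence of closure is named first.
- **A condensed article may leave a survival method to an analysis plan.** Silence alone would be no finding. Here the text assigns a different model to every outcome. If generalised linear mixed models were meant, the text does not say so, and that reading still names no method for censored times.

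**Conclusion.** Wrong as written, with unequal consequences. The substantive error is for time to healing: a linear model cannot represent censoring at week 12 or at loss to follow-up. The power cost runs from about 6–8 points (unhealed set to 12 weeks, nobody lost) to about 44 points (healed only), under an assumed constant hazard, assumed healing rates and 44 per group. The plan does not say which workaround would be used, so the larger figure must not be quoted as the expected loss. With 20% loss expected, neither workaround is correct.

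For complete closure, the model is misspecified (non-constant variance, fitted values outside 0–1, no estimable within-person random effect), but the group test is approximately valid in the settings simulated and the coefficient is an adjusted risk difference. The documents do not support a claim that the primary result would be invalid. For repeated ulcer area, PUSH and scale scores, the stated model is suitable.

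**What to change.** Before analysis, replace the single sentence in Data analysis with outcome-specific models:

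- **Complete closure at 12 weeks:** a binary regression (logistic or modified Poisson) with the prespecified covariates, reported with an adjusted risk difference and 95% CI so that the result is on the scale used for sizing.
- **Time to healing:** Kaplan–Meier curves and Cox regression, or a discrete-time or interval-censored model, since healing is seen only at scheduled assessments (weeks 2, 4, 6, 8 and 12 in Table 2). Censor unhealed participants at their last assessment.
- **Repeated continuous outcomes** (ulcer area, PUSH, scale scores): keep the linear mixed model.

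The cost is wording only. The fortnightly wound assessments already planned supply everything needed, and no visit, measurement or sample size changes.

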### Sample size calculations and expected loss to follow up

The sample size estimation was based on wound healing data from our pilot study and an estimated post-intervention difference in healing between groups. A sample of 44 participants randomised to each group will be sufficient to detect a moderate effect size difference (80% power and a 5% significance level) of 20% difference in proportions of healed ulcers between groups after a 12 week exercise intervention. This figure rises to 55 in each group to allow for a 20% loss to follow-up.

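### The stated 80% power for a 20-point difference with 44 per group does not reproduce unless the control healing rate is extreme; at control rates of 20–60% it is about 47–54%

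*Protocol article*

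**What the plan says.** The protocol article, under Sample size calculations and expected loss to follow up, makes one power statement. "A sample of 44 participants randomised to each group" is said to be "sufficient to detect a moderate effect size difference (80% power and a 5% significance level) of 20% difference in proportions of healed ulcers". On attrition it adds: "This figure rises to 55 in each group to allow for a 20% loss to follow-up". The source is described only in general terms: "The sample size estimation was based on wound healing data from our pilot study", together with an estimated difference after the intervention. No control healing proportion is printed.

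The endpoint is binary: complete wound closure, assessed "at the completion of the study (12 weeks after initiation of exercise intervention". The Data analysis section names chi-square for categorical variables and says "Statistical significance will be set at p < 0.05 for all analyses". Neither section says whether the test is one-sided or two-sided.

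**The concern.** A 20-point difference between two proportions in the middle of the scale usually needs well over 80 per group for 80% power at a two-sided 5% level. Forty-four is about half that. The paragraph also describes the target in two ways, as a moderate effect size and as a 20% difference in proportions, and the two need not be the same quantity.

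This is the article's only power statement, and it concerns ulcer healing, the primary outcome. A reader will use it to weigh a non-significant result. The text implies that a true 20-point benefit would be missed one time in five. If the control rate is in the middle of the scale, it would be missed about half the time.

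**Working it through.** **Inputs from the article.** 44 per group, 1:1; power 80%; significance level 5%; difference 20 percentage points; 20% loss to follow-up; binary endpoint at 12 weeks.

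**Assumed, because not printed.** Two-sided test (one-sided also tried). Control healing rate 20–60% for the main results, with the whole feasible range of 0–80% also scanned.

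**Step 1: the attrition step.** 44 / (1 − 0.20) = 55. This reproduces, so the 44 is the evaluable number and is the figure to check.

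**Step 2: power with 44 per group.** With control rate p1, p2 = p1 + 0.20 and p̄ their mean, the pooled-variance normal approximation is

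power = Φ{ [0.20·√n − 1.96·√(2p̄(1−p̄))] / √(p1(1−p1) + p2(1−p2)) }.

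Example, 50% v 70%: 0.20·√44 = 1.327; 1.96·√0.48 = 1.358; √(0.25 + 0.21) = 0.678. So Φ(−0.031/0.678) = Φ(−0.046) = 48.2%.

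The matching sample size is n = [1.96·√(2p̄(1−p̄)) + 0.842·√(p1(1−p1) + p2(1−p2))]² / 0.20². At 50% v 70% this is (1.358 + 0.571)² / 0.04 = 93 per group.

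| Control v intervention | Two-sided power, n = 44 | One-sided power, n = 44 | n per group for 80%, two-sided | Difference detectable at 80%, n = 44, two-sided |
|---|---|---|---|---|
| 20% v 40% | 53.6% | 66.0% | 82 | 28.0 points |
| 30% v 50% | 48.2% | 60.9% | 93 | 29.3 points |
| 40% v 60% | 46.6% | 59.3% | 97 | 29.4 points |
| 50% v 70% | 48.2% | 60.9% | 93 | 28.3 points |
| 60% v 80% | 53.6% | 66.0% | 82 | 26.2 points |

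**Step 3: other methods, same control range, two-sided.** Unpooled variance 48–56%; arcsine 47–55%; exact enumeration of the uncorrected chi-square test 45–55%; Fisher's exact test 36–45%. With all 55 per group evaluable, the pooled formula gives 56–63%. Reading the 20% as a relative difference gives 7–22%. None reaches 80%.

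**Step 4: where 80% does hold.** Two-sided, pooled: control rate about 3% or lower, or about 77% or higher. The arcsine formula moves these limits to about 5% and 75%. One-sided, pooled: about 8% or lower, or about 72% or higher. A 20-point rise is impossible above a control rate of 80%, so the upper window is narrow. Just inside the limits power is still short: 75.6% two-sided at 5% v 25% or 75% v 95%, and 65.5% at 10% v 30% or 70% v 90%.

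**Step 5: what 44 does match.** For a 2×2 chi-square test with 1 degree of freedom, 80% power at 5% needs N·w² = 7.849. Cohen's medium value w = 0.3 gives N = 7.849 / 0.09 = 87.2, hence 88 in total or 44 per group, with power 80.4%. With equal groups w = (difference/2) / √(p̄(1−p̄)), so at p̄ = 0.5 a w of 0.3 is a difference of 2 × 0.3 × 0.5 = 30 points. A 20-point difference is w = 0.20–0.22 over control rates of 20–60%. The other common index does not give 44: a medium Cohen's h of 0.5 needs 2 × 7.849 / 0.25 = 62.8, or 63 per group.

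**The case against.** The strongest reply is that the calculation is said to rest on pilot data that the article does not print. The 20–60% range is therefore the reviewer's, and sidedness is also open. A pilot control rate near 3% or 77% would make the statement correct, and a one-sided test would widen those windows to about 8% and 72%. This stands as a condition. A reader might infer that the 80% is wrong at every control rate, and the documents do not support that. They also do not indicate an extreme rate or a one-sided test, and the paragraph as printed gives no basis for the claim.

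A second reply is that 44 and 80% do follow from the paragraph's own phrase about a moderate effect, through w = 0.3. This also stands, and it changes the diagnosis: the 44 may be sound for the quantity that was entered, with the 20% label being the part that does not fit. The article names no index, so this origin remains an inference.

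Two stronger readings should be resisted. A reader may notice that some pairs of rates need about twice 44 per group and infer that a total was mistaken for a per-group number. Nothing in the article shows this, and w = 0.3 explains 44 as a correct half of 88. A reader may also infer that, even with an observed difference equal to the target, the 95% confidence interval would always reach zero. The Wald half-width at 44 per group is 18.7 points at 20% v 40% and 60% v 80%, which excludes zero. It is 20.0 at 30% v 50% and 50% v 70%, and 20.5 at 40% v 60%, so zero is just included only for control rates of about 30–50%.

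**Conclusion.** Wrong as written. The three figures, 44 per group, 80% power and a 20-point difference, fit together only at an extreme control healing rate that the article does not state. For control rates of 20–60%, a true 20-point effect would be detected about half the time with a two-sided test. The requirement for 80% power would be 82–97 evaluable per group against the stated 44. The conclusion rests on the assumed control range, equal allocation and 44 evaluable per group. It does not depend on the choice among the standard formulas, on a one-sided test, or on having no attrition, since none of these restores 80% within the range. The error lies in the stated operating characteristic. It does not alter any trial procedure or analysis.

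**What to change.** Rewrite the sample size paragraph so that it can be reproduced:

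- Print the pilot control healing proportion, the sidedness of the test and the effect-size index that was entered.
- Reconcile the moderate effect size with the 20% difference. The first phrase should not simply be deleted, because it may be what explains the 44.
- Then restate one of two things: the power for 20 points with 44 evaluable per group (about 45–55% two-sided if the control rate is 20–60%), or the difference detectable with 80% power (about 26–29 points over the same range).
- If the pilot rate was extreme enough to support 80%, printing it with the test used is sufficient.

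The attrition step to 55 per group needs no correction. The article reports the trial as being in follow-up, so this is a change of wording only and asks for no extra patients. The downside is a less favourable stated power or a larger stated detectable difference.
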